**Table S1 (SDC,**
https://links.lww.com/TXD/A839) details the estimands (including for the secondary outcomes) and associated intercurrent event strategies.

All statistical analyses will be stratified by graft type (kidney or simultaneous pancreas and kidney) and age group (<60 or ≥60 y) and adjust for site and other relevant covariates (eg, sex). Continuous covariates will be standardized within stratum (graft type/age group combination), and the reference value for categorical covariates will be set to the most frequently observed category. The analysis for the primary estimand will use a Bayesian proportional odds cumulative logistic regression model. The treatment effect (intervention compared with standard of care) will be reported as a posterior distribution of the common odds ratio of a higher ordinal category (ie, worse outcome). The reference stratum will be the combination of a kidney graft type and the <60 y age group. Model parameters will have weakly informative prior distributions including standard Gaussian distributions for the stratum, intervention and covariate parameters, and a Dirichlet distribution (concentration of 1) for the cut points.^20^

An exploratory model will assess treatment effect heterogeneity (across graft type and age group strata) with a stratum-specific treatment effect parameter and a 2-level hierarchical structure that allows for data-driven information borrowing across strata.^10^ The exploratory model estimates the common odds ratio for the intervention compared with standard of care in each stratum. Models for the secondary estimands include a linear model (for continuous outcomes, eg, change in eGFR), logistic model (for binary outcomes, eg, development of De novo donor-specific antibodies) and a Weibull survival model (for time to event outcomes, eg, time of allograft loss). The linear, logistic and survival models estimate the posterior distributions of the linear (additive) effect, odds ratio and hazard, respectively, for the intervention compared with standard of care. Weakly informative prior distributions will be used for all model parameters to support estimation while allowing flexibility.

The adaptive trial design includes prespecified interim analyses occurring after 100 participants reach the primary endpoint, and every 60 thereafter. Trial adaptations are based on the posterior probability that the common odds ratio from the primary estimand is <0.9 (ie, the common odds ratio that a participant allocated to the intervention arm will have a better ordinal outcome than a participant allocated to the standard-of-care arm). The trial will stop early for superiority or futility if this posterior probability exceeds 95% or falls below 10%, respectively.

Extensive simulations were conducted to inform key design parameters, including the maximum sample size (n = 280). These simulations evaluated the various scenarios of the treatment effects, the event rates, interim analysis timing, and intercurrent events. For each scenario, 5000 trials were simulated assuming 5% loss to follow-up by 12 wk after randomization. The modeling confirmed that the trial design maintains robust control of type 1 error while achieving adequate statistical power to detect clinically relevant treatment effects across a range of plausible assumptions.

All summary statistics, analyses, and data visualizations will be generated in R version 4.2.2 or later.^21^ A detailed description of the trial estimands, statistical models, decision criteria for adaptations and justification of the trial design by simulation are outlined in **Supplementary File 1** (**SDC**, https://links.lww.com/TXD/A839), with simulation results presented in **Figure S1 and Table S2** (**SDC**, https://links.lww.com/TXD/A839).

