### Primary Outcome

The primary outcome is a composite, ordinal outcome assessed at 12 wk (with an acceptable window of 11–13 wk) after randomization (Table 2; Figure 1). Each participant will be assigned to a category on a 5-point ordinal scale, with higher scores indicating worse outcomes:

**TABLE 2. T2:** Primary composite ordinal outcome at 12 wk postrandomization

Primary objective	Outcome measure(s)	Time-point(s)
To compare the efficacy of immunosuppression reduction/ modification strategies, with and without IVIg, on BKPyV infection in kidney and simultaneous kidney-pancreas transplantation recipients	A composite, ordinal outcome defined as: 5: All-cause death or allograft loss (kidney and/or pancreas) or eGFR decline ≥10 mL/min/1.73 m^2^ using the CKD-EPI formula^*a*^ for adults and the Schwartz formula^*a*^ for children 4: Acute rejection (kidney and/or pancreas) or BKV load >1000 copies/mL 3: Large reduction in immunosuppression relative to baseline 2: Moderate reduction in immunosuppression relative to baseline 1: Small to no reduction in immunosuppression relative to baseline Participants will be assigned a category between 1 (best) and 5 (worst).	Week 12

^*a*^ Pancreas graft function loss is defined as kidney-pancreas transplantion recipients’ insulin use is ≥0.5 units/kg/d for 90 consecutive days, or when the recipient’s pancreas graft is removed, and/ or re-registered for a pancreas transplantation.

BKPyV, BK polyomavirus; CKD-EPI, Chronic Kidney Disease Epidemiology Collaboration; eGFR, estimated glomerular filtration rate; IVIg, intravenous immunoglobulin; NB, all timepoints in the above table commence from the date of randomization.

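### The parenthesis in the interim stopping rule describes the common odds ratio in the opposite direction to the primary model; it needs rewording, with the thresholds unchanged

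*Protocol article*

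**What the plan says.** Three statements in the protocol article set the direction of the treatment effect.

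- **Primary Outcome** section: the five-level scale is scored "with higher scores indicating worse outcomes".
- **Statistical Analyses**, primary model: the effect of intervention against standard of care is reported as a "posterior distribution of the common odds ratio of a higher ordinal category (ie, worse outcome"). On this definition a ratio below 1 favours IVIg.
- **Statistical Analyses**, interim rule: adaptations use the "posterior probability that the common odds ratio from the primary estimand is <0.9". Taken together with its explanatory parenthesis, the threshold reads "is <0.9 (ie, the common odds ratio that a participant allocated to the intervention arm will have a better ordinal outcome", the comparison being with standard care.

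The thresholds follow: "The trial will stop early for superiority or futility if this posterior probability exceeds 95% or falls below 10%, respectively". The looks are "interim analyses occurring after 100 participants reach the primary endpoint, and every 60 thereafter", up to a maximum of 280 participants.

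**The concern.** Under proportional odds, the odds ratio of a better outcome is the reciprocal of the odds ratio of a worse one. The article therefore gives one quantity two opposite directions a paragraph apart, and the second description sits inside the decision rule. A value below 0.9 is benefit under the model's definition and harm under the parenthesis.

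This is the only numerical efficacy or futility criterion in the article. According to the Trial Oversight section, the DSMB makes recommendations and the steering committee takes the final decision, so people who did not write the model will have to interpret the probability. Whether a ratio above 1 means better or worse in an ordinal model depends on how the outcome and the model are coded, so the decision rule is where the direction most needs to be unambiguous.

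**Working it through.** **Step 1: direction.** Let OR_w be the common odds ratio of a higher (worse) category, intervention against standard of care, and OR_b that of a better one. Then OR_b = 1/OR_w.

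- Primary model definition: the event OR_w < 0.9 means the odds of a worse category are more than 10% lower on IVIg. A high probability of this event is evidence of benefit, so above 95% for superiority and below 10% for futility is coherent.
- Parenthesis taken as the definition: the event OR_b < 0.9 is the same as OR_w > 1/0.9 = 1.11. A high probability of this event is evidence of harm, so the same two labels would be attached to the wrong ends.

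**Step 2: what can be reproduced.** The look schedule agrees with the maximum sample size: 100 + 3 × 60 = 280. The article gives no numerical type I error, power, target odds ratio or category probabilities, so its operating characteristics cannot be reproduced.

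**Step 3: one posterior, read both ways.** From the article: 1:1 allocation and a standard Gaussian prior on the intervention parameter. Assumed: 20% of participants in each category, no covariates and no dropout. The approximate information on the log odds ratio is I = (n/12)(1 − Σp³).

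- At the third look, n = 220: Σp³ = 5 × 0.2³ = 0.04, so I = (220/12) × 0.96 = 17.6. With the prior, the posterior SD is 1/√18.6 = 0.232.
- Suppose the posterior is centred on OR_w = 0.6 (log −0.511), which favours IVIg. With log 0.9 = −0.105:
  - P(OR_w < 0.9) = Φ((−0.105 + 0.511)/0.232) = Φ(1.75), about 96%: stop for superiority.
  - P(OR_b < 0.9) = Φ((−0.105 − 0.511)/0.232) = Φ(−2.66), about 0.4%: stop for futility.

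**Step 4: the whole schedule.** The same approximation was simulated with 100,000 trials per scenario. Looks were at 100, 160, 220 and 280, with superiority tested at every look and futility at the first three. Two assumed category distributions were used: even (20% each) and skewed (10/15/20/40/15%). Ranges run across the two.

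| True OR_w | Model definition: superiority / futility | Parenthesis as definition: superiority / futility |
|---|---|---|
| 0.5 | 88–89% / 0.2% | 0% / 98–99% |
| 0.6 | 65–66% / 0.9% | 0% / 92–93% |
| 1.0 | 4% / 28–29% | 4% / 28–29% |
| 1.5 | 0.1% / 84–85% | 46–48% / 2% |
| 2.0 | 0% / 98–99% | 88–89% / 0.2% |

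The right-hand column is the left-hand column in mirror image. At no effect the two readings behave alike, so a check of type I error alone would not reveal a reversal. The percentages depend on the assumed categories; the reversal does not.

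**The case against.** The strongest reply is that the rule, read as a whole, already has a direction. The main clause refers to the ratio from the primary estimand, which the preceding text defines as the odds ratio of a worse category. The thresholds attach to the posterior probability for that ratio. On this view the parenthesis is a clumsy attempt to say that a value below 0.9 means intervention participants do better, and an explanatory aside does not replace the quantity it explains. This stands, and it limits the point to a wording error.

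A reader might go further and infer that the trial will declare IVIg superior when it is harmful, or that the program is reversed. The documents do not support that, for three reasons.

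- The Statistical Analyses section reports adequate power from 5000 simulated trials per scenario. A program coded to the parenthesis would almost never reach superiority under true benefit (right-hand column above), so it could not have produced that result. No power figures are given, so this is indirect evidence, but it points away from a reversal.
- The detailed decision criteria are placed in Supplementary File 1, which is not shown and may be worded correctly.
- The rule is not the only route to stopping. The Trial Oversight and Safety sections let the DSMB recommend early termination for efficacy or safety, with the final decision resting with the steering committee.

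The reply does not make the published sentence right. The article states a direction and states it wrongly, so this is not detail left to a fuller document.

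**Conclusion.** The contradiction is established from the text alone. The parenthesis in the interim rule gives the reciprocal of the odds ratio defined for the primary model, and only the primary model's direction fits the superiority and futility labels. Taken as the definition, the parenthesis would move the decision region from OR_w < 0.9 to OR_w > 1.11 and swap the two boundaries.

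The simulated percentages show what a hypothetical miscoding would do. They rest on assumed category probabilities, a normal approximation, no covariates and no dropout, and they do not describe the rule as planned. The conclusion is a wording error that needs correcting because of where it sits. It is not evidence of a reversed analysis or of a design that fails.

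**What to change.** Replace the parenthesis with wording such as: *ie, the odds of a higher (worse) ordinal category are more than 10% lower in the intervention arm than in the standard-of-care arm, so OR <1 favours IVIg*. Leave the 0.9, 95% and 10% thresholds unchanged.

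Then confirm the same direction in Supplementary File 1, the interim analysis code and the DSMB report template. A simple test is to run the interim code on a simulated dataset with a clear IVIg benefit and check that the posterior probability is high and is labelled superiority. A null dataset will not serve, because both directions behave alike there.

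The cost is one sentence and a short code check. Sample size, look schedule and model are unaffected.

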### Trial Oversight

The study will be conducted and coordinated by the Australasian Kidney Trials Network. The study will be conducted according to Good Clinical Practice guidelines and the reporting of results will follow the Consolidated Standards of Reporting Trials guidelines.^22^

The Australasian Kidney Trials Network will establish and manage key oversight bodies, including an independent Data and Safety Monitoring Board (DSMB), an Endpoint Verification Committee, and a Consumer Advisory Board. The DSMB, comprising independent experts in clinical trials, nephrology, infectious diseases, and biostatistics, will monitor participant safety and trial progress, and may recommend early termination because of efficacy or safety concerns. While the DSMB will report to the GSC Chair, all final decisions on trial modifications or early stopping will rest with the GSC.

### Safety

Participant safety will be closely monitored throughout the trial, with all AEs, adverse drug reactions, serious AEs, suspected unexpected serious adverse reactions, and AEs of special interest reported by site staff and reviewed by the DSMB. Investigators will assess the relationship between any adverse event and IVIg administration using a standardized scale (none, unlikely, possible, or probable). All safety data will be reviewed by the DSMB (**Table S2, SDC,**
https://links.lww.com/TXD/A839), which is responsible for evaluating participant safety and determining whether any trial modifications or early stopping are warranted.

### Data Security, Confidentiality, and Handling

All data collected in the BEAT-BK study will be stored securely in accordance with national regulations and the data management procedures outlined in the Country-Specific Appendices. Identifiable information will remain confidential and accessible only to the research team. Article-based documents will be stored in a locked facility, while electronic data will be maintained on a secure, access-restricted online platform. Personal information will be used solely for the study. Consent forms will be retained locally, and all study-related documentation, including ethics approvals and correspondence, will be archived for up to 15 y after trial closure or until the youngest participant reaches 25 y of age, whichever is later. Datasets will be made available to BEAT-BK investigators for approved substudies once the primary article is published. For external researchers, de-identified individual participant data may be accessed upon request to a dedicated Data Access Committee.

## DISCUSSION

The BEAT-BK trial addresses a key unmet need in kidney and SPK transplant recipients, as BKPyV infection is a clinically significant complication that can result in progressive graft dysfunction and loss. Immunosuppression reduction aims to restore BKPyV-specific cellular immunity, thereby facilitating viral clearance. However, this approach is not without risks. Inadequate immunosuppression may result in both acute and chronic rejection, leading to irreversible graft injury and potential graft loss. IVIg has been proposed as a potential therapeutic candidate because of its immunomodulatory and antiviral properties. Observational evidence suggested that IVIg has been associated with a rise in genotype-specific neutralizing antibody responses to BKPyV infections and, therefore, a reduced risk of BKPyVAN in high-risk populations. However, the lack of high-quality evidence has precluded definitive conclusions regarding the clinical efficacy of this treatment in treating BKPyV infection in transplant recipients. Also, IVIg is associated with known risk, including hypersensitivity reactions, thromboembolic events, acute kidney injury, and fluid overload, and carries a significant financial cost.

Using a novel Bayesian adaptive design, the trial framework enables planned interim analyses and sample size re-estimation, facilitating timely decisions regarding trial continuation or early stopping for efficacy or futility. More importantly, it enables efficient resource allocation, directing efforts toward the most promising treatment strategies and exposing fewer patients to inferior treatments. The selection of a 12-wk endpoint reflects a clinically meaningful timeframe for assessing early viral clearance, immunological and graft-related outcomes. In the absence of approved and effective antiviral treatments for BKPyV infection, the findings of the BEAT-BK trial will provide critical evidence to guide therapeutic decision-making. If found to be effective, IVIg could offer a viable strategy to improve long-term graft outcomes in kidney and SPK transplant recipients. If IVIg is deemed ineffective, the trial findings will then support de-implementation of an expensive and ineffective treatment, thereby avoiding unnecessary exposure to potential harms.
